#### Secondary endpoints

Secondary endpoints of PAD outcomes are based on the Society for Vascular Surgery (SVS) reporting standards [17]:
Amputation-free survival; defined as time spent free from any major above ankle amputation [17]Hemodynamic improvement: defined as an increase in the ABI by at least 0.10 [17]Clinical improvement: which is defined as an upward shift by at least one Rutherford category. However, PAD patients suffering from actual tissue loss (Rutherford category 5 [19]) should move up two Rutherford categories to be considered improved [19].Re-intervention or stenosis rate; any re-intervention or stenosis among patients who already underwent vascular surgery [17]Freedom from major adverse cardiovascular events (MACE). MACE is defined as any major cardiovascular event such as myocardial infarction, cerebrovascular accident or death [17].Major adverse limb events (MALE). MALE is defined as any major amputation or revascularization procedure [17].Revascularisation-free survival; defined as time free from any revascularisation procedure regardless of if it were an endovascular intervention or an open surgery [17].Change from baseline of the following risk factors:
a-BMI (measured in kg/m^2^)b-HbA1c (measured as a percentage)c-Total cholesterol (measured in mmol/L)Health-related quality of life [18]; assessed using the Dartmouth Cooperative Information Project (COOP) charts at enrolment and after 1 year. The COOP charts measure six core aspects of functional status: physical fitness, feelings, daily activities, social activities, change in health, pain, and overall health. The instrument consists of six charts, referring to the abovementioned aspects of functioning. Each chart consists of a simple title, a question referring to the status of the patient and an ordinal 5-point response scale illustrated with a simple drawing. Each item is rated on this 5-point ordinal scale ranging from 1 (no limitation at all) to 5 (severely limited); for “change in health” score 1 means “much better” and score 5 “much worse”. The designers do not advocate summing the responses to gain a single index figure of health status

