## Background

Peripheral arterial disease (PAD) affects more than 200 million of the global population [1]. PAD represents a marker for premature cardiovascular events [2]. Patients with PAD, even in the absence of a history of myocardial infarction or ischemic stroke, have approximately the same relative risk of death from cardiovascular causes as patients with a history of coronary or cerebrovascular disease [2]. Despite the high prevalence of PAD and the strong association with cardiovascular morbidity and mortality, patients with PAD are less likely to receive appropriate treatment for their atherosclerotic risk factors than those who are being treated for coronary artery disease [3, 4].

As PAD represents a peripheral manifestation of atherosclerosis, most traditional and novel cardiovascular risk factors are strongly associated with this condition [5–7]. Smoking, diabetes, hyperlipidaemia, hypertension, unhealthy diet and physical inactivity were identified as significant modifiable risk factors that should be targeted for secondary prevention [8–12].

Atherosclerotic risk factor identification and modification play an important role in reducing the number of adverse outcomes among patients with atherosclerosis [13]. Risk reduction therapy decreases the risk of cardiovascular mortality and morbidity in patients with PAD [13]. Because of the efficacy of these techniques, several expert committees have recommended their use in patients with PAD [8–12]. Despite clear guidelines, several studies have shown that patients with PAD are routinely undertreated for these risk factors [4], which may contribute to high rates of morbidity and mortality.

Previous studies concluded that modifiable risk factor programmes help cardiac patients achieve their risk factor modification targets, with subsequent reduction in cardiovascular events [14–16]. To our knowledge, currently, there is still no evidence to support that the implementation of a structured modifiable risk factor reduction program will lead to improved outcomes in PAD patients. However, due to the similar atherosclerotic burden in cardiac and PAD patients, we hypothesise that these risk factor modification programmes would similarly improve risk factor target achievement in PAD patients and subsequently improve their clinical outcomes and reduce their amputation rates when compared to standard healthcare.

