## Methods

### Study design

This is a randomised, parallel group, active-control trial to compare the effectiveness of the risk factor modification intervention programme to standard healthcare in a tertiary vascular care centre, in the reduction of the prevalence of modifiable risk factors in PAD patients.

This trial will randomise patients with PAD in an equal ratio to one of two treatment arms. One arm will be randomised to undergo a risk factor modification intervention programme at a community-based centre. The other arm will be provided with standard healthcare advice, in the outpatient PAD clinic in a tertiary referral vascular centre. Patients randomised into the risk factor modification intervention programme will have the intervention administered for 12 weeks. Patients will then be followed for 12 months to determine further PAD outcomes. The participant flowchart through the study is shown in Fig. 1. SPIRIT figure for this trial is given in Fig. 2.

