### Sample size calculation

For sample size calculation, the EUROACTION study [30] was used to estimate the coefficient of variation for sample proportions.

Data from the EUROACTION [30] study suggest that 12-week intervention response rates for the primary endpoint of 54.8% (intervention programme) and 35.6% (usual care). Eighty percent statistical power and an alpha level of 5% were chosen. A two-sample comparison of proportions sample size calculation was implemented.

With these parameters, the G*Power [31] software yields a trial with a maximum sample size of 208 patients completing the intervention (104 per intervention group).

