### Statistical analysis

All data will be analysed according to the intention to treat principle. The primary outcome, the achievement of treatment goals for PAD risk factors between both groups at 12 weeks and 12 months will be compared using chi-square or Fisher’s exact where appropriate. Secondary outcomes including time to event will be assessed using Kaplan-Meier survival curves and log rank test. An exact 95% confidence interval will be applied for the difference between intervention groups in terms of PAD risk factor reduction.

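### Amputation-free and revascularisation-free survival leave out death, so Kaplan-Meier estimates under these names exceed survival free of both death and the limb event

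*Protocol article*

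**What the plan says.** The Secondary endpoints section of the protocol article defines two endpoints that carry the word survival:

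- "Amputation-free survival; defined as time spent free from any major above ankle amputation"
- "Revascularisation-free survival; defined as time free from any revascularisation procedure regardless of if it were an endovascular intervention or an open surgery"

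Neither names death. Another item in the same list does: "MACE is defined as any major cardiovascular event such as myocardial infarction, cerebrovascular accident or death".

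The Statistical analysis section has one sentence on how such outcomes are analysed: "Secondary outcomes including time to event will be assessed using Kaplan-Meier survival curves and log rank test". It gives no rule for patients who die and mentions no competing-risk method. The abstract and the Secondary objectives section also list amputation-free survival, without adding death to it.

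On follow-up, the Study design section says: "Patients will then be followed for 12 months to determine further PAD outcomes".

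**The concern.** An endpoint called amputation-free survival is read as the proportion of patients alive without a major amputation. As defined, it is the proportion without a major amputation, whatever their vital status. If death is not an event, Kaplan-Meier can only end that patient's follow-up at death, and the estimate carries on as if the patient could still lose or keep the limb. The same holds for revascularisation-free survival.

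The article itself gives reason to think that death matters here. The Background says that patients with PAD "have approximately the same relative risk of death from cardiovascular causes as patients with a history of coronary or cerebrovascular disease", and that risk-reduction therapy lowers cardiovascular mortality in them. Death is therefore an outcome that the programme might change, and these two endpoints cannot register it. At stake are the absolute 1-year figures, which would be published under a name that they do not satisfy, and what the log-rank test on these endpoints is able to detect.

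**Working it through.** **The plan's own figure.** The article gives no event rate, mortality or power for the time-to-event endpoints. Its only computed figure is 208 patients (104 per arm), from response rates of 54.8% and 35.6% with 80% power and 5% alpha. It reproduces two-sided: 105 per arm by the pooled z-test, 104.1 by the arcsine method, and 79.9% power at 104 per arm. It concerns the primary endpoint and does not bear on this point. I use 104 only to turn percentages into patients.

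**Inputs.** Let a be the 1-year risk of the limb event and d the 1-year mortality. Neither is in the documents. Assumed: a = 5% (amputation) or 20% (revascularisation); d = 2%, 5% or 10%.

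**Formulas**, with constant independent hazards over one year:

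- Limb event only, deaths censored: S = 1 - a
- First of limb event or death: S = (1 - a)(1 - d)
- Excess: (1 - a) - (1 - a)(1 - d) = (1 - a)d

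**Results**

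| Endpoint | a | d | As written | Death counted | Excess (points) | Patients per 104 |
|---|---|---|---|---|---|---|
| Amputation | 5% | 2% | 95.0% | 93.1% | 1.9 | 2.0 |
| Amputation | 5% | 5% | 95.0% | 90.25% | 4.75 | 4.9 |
| Amputation | 5% | 10% | 95.0% | 85.5% | 9.5 | 9.9 |
| Revascularisation | 20% | 2% | 80.0% | 78.4% | 1.6 | 1.7 |
| Revascularisation | 20% | 5% | 80.0% | 76.0% | 4.0 | 4.2 |
| Revascularisation | 20% | 10% | 80.0% | 72.0% | 8.0 | 8.3 |

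The smallest excess is 0.80 x 0.02 = 1.6 points and the largest is 0.95 x 0.10 = 9.5 points. It is above zero whenever anyone dies before the limb event.

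**Share of first events that still count.** This is ln(1 - a) / [ln(1 - a) + ln(1 - d)]:

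- a = 5%, d = 2%: 0.0513 / 0.0715 = 72%
- a = 20%, d = 5%: 0.2231 / 0.2744 = 81%
- a = 5%, d = 10%: 0.0513 / 0.1567 = 33%

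So the loss of events ranges from modest to most of them, depending on whether deaths outnumber limb events.

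**If freedom from the limb event alone is the target.** The comparator is then 1 minus the cumulative incidence with death competing. At a = d = 5%, each cause has half of the first events, so cumulative incidence is 0.5 x (1 - 0.9025) = 4.875% and its complement is 95.1%. The censored estimate of 95.0% is slightly below that, not above it.

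**Between arms.** Suppose a = 5% in both arms, with mortality 5% in one and 10% in the other. As written, both arms show 95.0%. With death counted, they show 90.25% and 85.5%, a difference of 4.75 points. The arm with the lower mortality gets no credit, and that could be either arm.

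**The case against.** The best counter-argument is that the article never says that deaths are censored. Event and censoring rules usually sit in the SAP or full protocol, which are not shown, and the definitions are attributed to cited reporting standards that are not at hand. The wording could be shorthand. That stands as a caution about what the trial will actually do. It does not remove the point: the definitions are stated, they differ from the MACE definition in the same list, and an SAP that counted death would contradict them.

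It can also be said that the size rests wholly on assumed rates, and that mortality may be low. The eligibility criteria start at Rutherford category 2 and exclude immobile patients and those with comorbidity such as ischaemic heart failure or severe kidney disease. That stands, and is why the range starts at 2%.

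Four stronger readings are tempting, and the documents do not support them:

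- *Most of the log-rank events are lost.* This is true only where deaths outnumber limb events; elsewhere in the assumed range, 72% or 81% are kept.
- *An arm in which frail patients die early will look better.* This needs deaths that differ by arm and are correlated with limb risk. With independent hazards, a log-rank test that censors deaths is a valid comparison of the limb-event hazard.
- *MALE and need for revascularisation share the fault.* Nothing says that they will be reported as 1 minus Kaplan-Meier, and MALE has no time-to-event definition.
- *The trial ignores deaths.* It does not: freedom from MACE includes them.

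**Conclusion.** The point holds as one of definition. The two endpoints are named for survival and defined without it, and with the stated method the reported figure exceeds survival free of both events by (1 - a)d. That is about 1.6 to 9.5 percentage points for assumed a of 5% to 20% and d of 2% to 10%, with independent constant hazards. The documents supply no mortality or limb-event rate, so the true size is unknown. The excess is relative to the composite; for limb-event freedom alone the numerical error is small, but the name is then wrong. The effect on the comparison between arms has no fixed direction. The primary endpoint and the sample size of 208 are untouched. Severity is moderate.

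**What to change.** Define each endpoint as the time from randomisation to whichever comes first: death from any cause, or the limb event (major above-ankle amputation for one, any revascularisation for the other). Kaplan-Meier and the log-rank test can then stay as planned.

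If freedom from the limb event alone is what is wanted, drop the word survival from both names and report cumulative incidence with death as a competing event. Show mortality by arm beside it, because cumulative incidence itself falls as competing deaths rise.

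The cost is a wording change in the endpoint section, carried into the SAP and documented before unblinding. Deaths are already captured as part of MACE and the One-year assessment covers MACE, so no new outcome is needed. The sponsor should confirm that the date of death is recorded. The sample size does not change.

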### Secondary objectives

Secondary objectives are to compare the impact of the programme on clinical outcomes in PAD patients, specifically:
Amputation-free survivalClinical improvement [17]Haemodynamic improvement [17]Need for revascularisation proceduresChanges in quality of life [18]The incidence of adverse events

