### Baseline, prior to intervention

All randomised patients will undergo a full baseline assessment prior to their intervention:
PAD assessment;
Ankle-brachial index (ABI)Digital pressureRutherford category [19]Wound ischaemia and foot infection classification (WIfI) [22]Blood samples including:
Fasting blood lipidsFasting glucoseHbA1cBlood pressure documentationAnthropometric measurements including:
BMIWaist circumferenceSub-maximal functional capacity exercise testing including:
Shuttle test [23]Claudication distance [24]Absolute walking distance [25]Behavioural and psychological survey using the Hospital Anxiety and Depression Scale (HADS) [26].Health-related quality of life assessment: Dartmouth Quality of Life score [18].Smoking status assessment using the Fagerstrom Test for Nicotine Dependence [27].Physical activity assessment: Godin and Shepard Leisure Exercise Questionnaire [28].Nutritional assessment through the Mediterranean Diet Questionnaire [29].

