#### Twelve-week assessment

On completion of the 12 weeks in both groups, patients are reassessed for risk factors, therapeutic management and lifestyle changes similar to baseline.

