#### One-year assessment

Similar to the baseline and 12-week assessment, in addition to clinical outcomes assessment, the following are included:
If the patient underwent a major amputation and level of amputationIf required a revascularisation procedure.Any residual stenosis of more than 30% [17]If developed a major adverse cardiovascular event (MACE) or major adverse limb event (MALE)Health-related quality of lifeCost-effectiveness of the programme

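### Haemodynamic status is analysed only as an ABI rise of at least 0.10, so a fall counts as no change; a baseline-adjusted ABI comparison should be added

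*Protocol article*

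**What the plan says.** The Secondary endpoints section of the protocol article defines two limb-status measures as responder endpoints. One is "Hemodynamic improvement: defined as an increase in the ABI by at least 0.10". The other is "Clinical improvement: which is defined as an upward shift by at least one Rutherford category", with a two-category shift required for patients with tissue loss. Neither has a worsened level. Both come under the opening statement "Secondary endpoints of PAD outcomes are based on the Society for Vascular Surgery (SVS) reporting standards".

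The same section has an item headed "Change from baseline of the following risk factors". It names BMI, HbA1c and total cholesterol, but neither ABI nor Rutherford category.

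ABI and Rutherford category are both in the list under Baseline, prior to intervention. The One-year assessment is described as "Similar to the baseline and 12-week assessment, in addition to clinical outcomes assessment", which implies that both are measured again at 1 year. Major amputation and revascularisation are counted separately, in amputation-free survival, revascularisation-free survival and MALE.

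**The concern.** ABI is a continuous measurement taken before and after. Reducing it to whether it rose by 0.10 has two effects. First, a fall of 0.20 and no change at all both score as not improved. Second, the size of any change is ignored, which costs precision.

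The Background section expects the programme to improve clinical outcomes and reduce amputation rates, and the article states "Secondary objectives are to compare the impact of the programme on clinical outcomes in PAD patients". Better risk-factor control could plausibly act partly by slowing progression. If so, neither responder endpoint can show it unless the patient reaches amputation or a procedure. The protocol already uses change from baseline for three risk factors, so leaving ABI out gives its objective limb measure the coarser treatment.

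**Working it through.** **The article's own figure.** The only sample size given is for the primary endpoint: 54.8% v 35.6%, 5% alpha, 80% power, 104 per group. With pooled variance, two-sided and without continuity correction:

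n = [1.96 × √(2 × 0.452 × 0.548) + 0.842 × √(0.548 × 0.452 + 0.356 × 0.644)]² / 0.192² ≈ 104.3, that is 105 per group. Power at 104 per group is 79.9%. The stated size reproduces, but it says nothing about ABI. Below it supplies only the arm size of 104.

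**Information kept by one cut.** Take ABI change as normal with the same SD in both arms. For small arm differences, the efficiency of the responder comparison relative to a comparison of mean change is

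ARE = φ(c)² / [p(1 − p)],

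where p is the share improved, c = z(1 − p) and φ is the standard normal density.

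The best case is p = 0.5: φ(0)² / 0.25 = 0.637, a loss of 36%. Any other share loses more: 42% at p = 0.30, 51% at p = 0.20, 66% at p = 0.10 and 78% at p = 0.05.

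**In terms of SD.** The article gives no SD, mean change or expected responder share for ABI, so the SDs below are assumed. With no mean change, c = 0.10/SD.

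| Assumed SD of change | c | Share rising ≥ 0.10 | ARE | Loss |
|---|---|---|---|---|
| 0.08 | 1.25 | 11% | 0.353 | 65% |
| 0.10 | 1.00 | 16% | 0.439 | 56% |
| 0.12 | 0.83 | 20% | 0.492 | 51% |
| 0.15 | 0.67 | 25% | 0.541 | 46% |
| 0.20 | 0.50 | 31% | 0.581 | 42% |

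**In terms of power.** 104 per arm, two-sided 5%, control mean change 0, assumed between-arm difference 0.05:

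| Assumed SD | Responder rates (control v programme) | Power, responder | Power, mean change |
|---|---|---|---|
| 0.10 | 15.9% v 30.9% | 73% | 95% |
| 0.15 | 25.2% v 36.9% | 44% | 67% |
| 0.20 | 30.9% v 40.1% | 29% | 44% |

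**Rutherford category.** The ABI formula does not carry over, because the measure is ordinal and the article gives no category distribution. Simulation with a three-level change (worse, same, improved), 104 per arm and 40,000 trials, all rates assumed (control v programme), gives:

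| Worsened | Improved | Power, responder | Power, Wilcoxon |
|---|---|---|---|
| 25% v 10% | 25% v 25% | 5.1% | 35.4% |
| 20% v 10% | 25% v 38% | 52.2% | 70.5% |
| 10% v 10% | 25% v 38% | 52.7% | 38.4% |
| 20% v 20% | 25% v 38% | 52.5% | 28.8% |

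The ordinal test gains when worsening is prevented and loses when benefit comes only through improvement.

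**The case against.** **The definitions follow a cited reporting standard and are applied consistently, so nothing is misstated.** This stands, and is why the responder definitions should be kept. But a standard for reporting does not require the responder rate to be the only between-arm comparison.

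**An ABI model may sit in a statistical analysis plan that is not shown.** It may. The point here is the endpoint list, which the article does fix: change from baseline is named for three measures, and ABI is not among them.

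**Stronger readings that a reader might infer are not supported:**

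- That nearly half the ABI information is thrown away. That figure fits only some assumed SDs. The raw values are collected, so information is left out of the named endpoint but not lost from the trial.
- That measurement noise alone marks 16% to 31% of unchanged patients as improved. Those shares come from SDs of 0.10 to 0.20 for total change, which mixes real change with error. If the error SD of change were 0.05 or 0.07 (assumed), the shares would be about 2% or 8%. The article gives no repeatability figure.
- That deterioration goes unseen. Severe worsening enters MALE, amputation-free survival and revascularisation-free survival. The COOP charts and adverse events may reflect functional decline. Only lesser worsening lacks a limb-status endpoint.
- That the Rutherford comparison should become ordinal. The last two simulated scenarios show that this can reduce power.
- That 12-week ABI is certainly available. The Twelve-week assessment says "patients are reassessed for risk factors, therapeutic management and lifestyle changes similar to baseline" without naming ABI, and the schedule figure is not shown. The fix therefore uses 1-year ABI.

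**Conclusion.** The point holds as a minor, inexpensive improvement. As written, the secondary endpoints treat a fall in ABI as no change, and they give worsening short of amputation or a procedure no limb-status endpoint. Under a normal model the 0.10 cut loses at least about 36% of the information in ABI change, whatever the SD. Over assumed SDs of 0.08 to 0.20 with no mean change, the loss is roughly 40% to 65%. The floor rests on the normal, common-SD model; the range also rests on SDs that the article does not supply. For Rutherford category the case extends only to reporting worsening, not to changing the test. The primary endpoint and its conclusion are unaffected.

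**What to change.** 1. Keep the responder definitions for ABI and Rutherford category, and the responder comparison for Rutherford, as they are.
2. Add ABI to the change-from-baseline list, with a prespecified between-arm ANCOVA of 1-year ABI on arm and baseline ABI.
3. Report by arm the proportions improved, unchanged and worsened for both ABI and Rutherford category.
4. State how patients who die, or have an amputation or revascularisation before the 1-year assessment, enter these analyses. A procedure can itself change ABI and Rutherford category.

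The cost is one extra secondary analysis, a descriptive table and a protocol wording change, with no new visits or tests if ABI is measured at 1 year as implied. The Discussion section sends important modifications first to the ethics committee and then to the registries and journal, so the change should follow that route if it is judged important. It should be settled before the allocation is unblinded.

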### Eligibility criteria

#### Inclusion criteria

Aged 18 years or moreProvide written informed consentPAD: diagnosed by at least one of the following:
Ankle-brachial index of less than 0.90 in at least one lower extremity [9]Toe brachial index of less than 0.60 [9]Evidence of arterial occlusive disease in one lower extremity detected by duplex ultrasonography, computed tomographic angiography, or magnetic resonance angiography [9]Symptomatic PAD (Rutherford category 2 and above [19])Patients should have at least one of the following risk factors:
Blood pressure > 140/80 mmHgFasting blood sugar (FBS) > 53 mmol/molGlycosylated haemoglobin (HbA1c) > 7%Total cholesterol > 5 mmol/LLow-density lipoprotein (LDL) cholesterol > 2.6 mmol/LTriglycerides > 1.7 mmol/LHigh-density lipoprotein (HDL) < 1.0 mmol/L in men and < 1.2 mmol/L in womenPhysical activity less 30 min for 5 days per weekBody mass index (BMI) > 25 kg/m^2^Waist circumference > 80 cm in women, and > 94 cm in menCurrent smoker or exposure to tobacco in any formUnhealthy diet, Mediterranean diet score less than 10 points

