### Study screening

Patients with Symptomatic PAD (Rutherford category 2 and above [19]) will be invited to join the study. Invited patients will be provided with a pre-designed information leaflet. This leaflet will be fully explained to the patient at the initial assessment. The study researchers will answer any questions about the study. Informed consent will be obtained from the patient on a formatted consent form. Patients will be given the freedom to give consent either on the same day or at a later date in accordance with a study within a trial (SWAT), entitled “Same-day Consent vs Delayed Consent in a Randomised Trial: A Study within a Trial” [21]. This SWAT aims to ensure the rigorousness of the consent process and will run in conjunction with this randomised controlled trial.

Researchers will screen the patient for inclusion and exclusion criteria and administer a series of the following:
Record PAD risk factors such as smoking, hyperlipidaemia, diabetes, hypertension, increased body weight and the patient’s current medication.Document the Rutherford category [19], claudication distance and absolute walking distance for each patient, to assess the severity of PAD.Schedule appointments for baseline health assessments over the following month.

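### As written, a limb procedure already decided at screening would count as a secondary-endpoint event, which would dilute the revascularisation and MALE comparisons without biasing them

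*Protocol article*

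**What the plan says.** **Entry.** Under Study screening, "Patients with Symptomatic PAD (Rutherford category 2 and above [19]) will be invited to join the study". The Inclusion criteria repeat that threshold and set no upper limit. Patients come from the outpatient PAD clinic of a tertiary vascular centre (Study setting, Study design). The clinical-improvement endpoint provides for severe disease: "PAD patients suffering from actual tissue loss (Rutherford category 5 [19]) should move up two Rutherford categories to be considered improved".

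**Exclusions.** The list has eight items. None concerns a revascularisation or amputation already decided or listed. The nearest are immobility and a comorbidity that could affect participation or outcomes.

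**Events.** Under Secondary endpoints, "MALE is defined as any major amputation or revascularization procedure". The time-to-event counterpart is "Revascularisation-free survival; defined as time free from any revascularisation procedure regardless of if it were an endovascular intervention or an open surgery". Amputation is worded alike: "Amputation-free survival; defined as time spent free from any major above ankle amputation". The One-year assessment asks whether a revascularisation was required and does not separate needs that existed at entry.

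**Allocation and analysis.** Randomisation is simple and 1:1 (Randomisation). Time-to-event secondary outcomes are compared with Kaplan-Meier curves and a log-rank test, with no strata named (Statistical analysis).

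**The concern.** One secondary objective is the programme's impact on the need for revascularisation. A need established before allocation says little about that. A mobile patient already listed for revascularisation could be randomised, treated shortly afterwards, and become an event in both MALE and revascularisation-free survival. The timetable leaves room for this: baseline appointments are booked over the month after screening, and randomised patients have their baseline assessment before the programme starts. A listed procedure could thus fall after randomisation but before any exposure to the programme.

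Such events would occur at similar rates in both arms. They would pull the risk ratio towards 1 and add noise to limb comparisons that the trial was not sized for.

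**Working it through.** **Step 1: the plan's own figure.** Inputs from Sample size calculation: 54.8% v 35.6%, 80% power, 5% alpha (taken as two-sided). With pooled variance, mean proportion 0.452 and difference 0.192:

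n = [1.96 × √(2 × 0.452 × 0.548) + 0.842 × √(0.548 × 0.452 + 0.356 × 0.644)]² / 0.192² = 104.3

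That is 105 per arm, 210 in total. The stated 104 per arm gives 79.9% power, so the 208 reproduces. It rests on the primary risk-factor endpoint and does not depend on this point.

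**Step 2: does the text count these procedures?** Taken together, entry has a floor and no ceiling, no exclusion refers to a procedure already decided, and the definitions take any procedure. A pre-decided revascularisation carried out after randomisation is an event on the stated wording.

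**Step 3: dilution, on assumed inputs.** The documents give no limb event rates and no share of pre-decided procedures. Let q be the share with a pre-decided procedure that takes place in both arms, r = 20% the control risk in the rest, and 0.50 the true risk ratio (RR) in the rest.

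- Control rate: pc = q + (1 − q) × 0.20
- Programme rate: pt = q + (1 − q) × 0.10
- Power = Φ{[(pc − pt)√n − 1.96√(2p̄(1 − p̄))] / √[pc(1 − pc) + pt(1 − pt)]}, where p̄ is the mean of pc and pt

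For q = 10%: pc = 0.28, pt = 0.19, RR = 0.68, and power = Φ[(0.918 − 1.175)/0.596] = Φ(−0.43) = 33%.

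| q | Control v programme | Observed RR | Share of control events pre-decided | Power, 104 per arm |
|---|---|---|---|---|
| 0 | 20.0% v 10.0% | 0.50 | 0% | 52% |
| 5% | 24.0% v 14.5% | 0.60 | 21% | 41% |
| 10% | 28.0% v 19.0% | 0.68 | 36% | 33% |
| 20% | 36.0% v 28.0% | 0.78 | 56% | 23% |
| 30% | 44.0% v 37.0% | 0.84 | 68% | 18% |

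A second set of assumptions has 95% of pre-decided procedures occurring in both arms, and 20% v 12% in the rest (true RR 0.60). For q = 10% the rates are 0.095 + 0.180 = 27.5% and 0.095 + 0.108 = 20.3%, RR 0.74. For q = 20% and 30% the RR is 0.82 and 0.87. The direction is the same.

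**Step 4: what restriction would recover.** Under the first set of assumptions, leaving out patients with a pre-decided procedure leaves 104 × (1 − q) per arm at 20% v 10%. For q = 10% that is 93 per arm and 48% power, against 33% for all procedures. For q = 20% it is 83 per arm and 44%, against 23%. The loss of patients is outweighed by the removal of dilution.

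**Step 5: disease severity.** Simple randomisation does not control the severity mix. If 20% had rest pain or tissue loss, with 60% events against 10% in claudicants (assumed), that fifth would supply 0.12 / (0.12 + 0.08) = 60% of events. The 95% range of chance imbalance is 1.96 × √(0.2 × 0.8 × 2/104) = ±10.9 points, worth up to 0.109 × 0.50 = 5.4 points in event rate. Stratifying the test removes this source of noise.

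**The case against.** **Silence is not enrolment.** Nothing in the article says that patients with a listed procedure are enrolled. It condenses a full protocol, and its abbreviations point to an analysis plan and a blinded report planning meeting where event-counting rules may sit. This stands as a limit on size. It does not remove the point, because the article itself prints the eligibility list and the endpoint definitions, and their wording is unrestricted.

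**Existing exclusions already screen some out.** Immobility, comorbidity and refusal of part of the intervention, together with weekly exercise classes and a shuttle test, probably remove some patients awaiting amputation. This stands: the point is weaker for amputation than for revascularisation.

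**A listed procedure can still be affected.** An elective procedure in a claudicant might be deferred or cancelled if symptoms improve, and that would be a genuine programme effect. This stands. It is why such events should stay in the main analysis, and why a near-certain procedure in both arms is an unfavourable assumption.

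**Stronger readings.** A reader might infer that the limb results would be biased, or that a chance imbalance could pass for an effect. The documents support neither. Allocation is random, so the pre-decided share is equal in expectation, and the log-rank test already allows for chance imbalance in its error rate. The 5.4-point shift in Step 5 also lies within the ordinary sampling range for a 20% event rate, 1.96 × √(2 × 0.2 × 0.8/104) = ±10.9 points. A reader might further infer that pre-decided procedures should be struck from the endpoint. That would leave a patient who has just been revascularised counted as event-free, and it would discard cancellations that the programme brought about.

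**Low power regardless.** Even with q = 0, 20% v 12% has about 35% power at 104 per arm. True: the fix makes these comparisons clearer but does not make them confirmatory.

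**Conclusion.** The point holds in a limited form. On the stated criteria and definitions, limb procedures decided before randomisation would be events in MALE and revascularisation-free survival, and they would be largely unrelated to allocation. The effect is dilution and lost precision in secondary comparisons. Under assumed shares of 5% to 30%, a true risk ratio of 0.50 would be seen as 0.60 to 0.84, and power would fall from 52% to between 41% and 18%. Every one of these inputs is an assumption. The actual share is unknown and could be close to nil, in which case the effect is negligible. The primary endpoint and the sample size are unaffected.

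**What to change.** 1. In Statistical analysis, stratify the log-rank tests by the Rutherford category already documented at screening (2–3 v 4 and above). No new data are needed.
2. Add one item to the screening form, completed before allocation: is a revascularisation or amputation already decided or listed (yes/no)? For patients already enrolled, take it from clinic records dated before randomisation, abstracted by someone blind to allocation.
3. Keep the all-procedures intention-to-treat definition for the main analysis. Add a pre-specified sensitivity analysis of MALE and revascularisation-free survival restricted to patients with no procedure decided at randomisation. Because the restriction uses a pre-randomisation characteristic, the comparison stays randomised, and no patient is counted as event-free after an uncounted procedure.

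Eligibility, treatment and sample size do not change. The cost is one form item, a retrospective records check for enrolled patients, one extra analysis, and fewer patients in that analysis. The wording should be fixed while the statistician is still blinded.
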